**Fig. 2 Fig2:**
[figure not shown]
Flow diagram

### Unblinding

For our study, unblinding is not of crucial importance as this study does not execute a drug trial. Yet, we shall take care of the unblinding procedure. Unblinding at any stage of the trial shall be done by an independent statistician not involved in the main trial so that other blinded procedures may not be affected. After an alert is raised by the on-site physician, the principal investigator shall analyze the situation and call for the unblinding. The database containing the results of the nested study and their corresponding data from the main trial of the unblinded participants will be emailed to the statistician who will further process the data.

### Intervention

The Health Belief Model is used to create the content of the study modules (Table 1). Expert consultations in the domains of behavioral sciences, health education, information technology, cardiac medicine, and hypertension management were sought in the development of these modules. The goal of these interventions is to control systolic blood pressure among study participants after 12 months.

**Table 1 Tab1:** Description of the different arms with intervention

**Arms**	**Components**	**Description**
**Ed-counseling intervention**	**Educational support** (educational booklet with animated infographics)	1) Ensuring that professionals are available throughout the continuum of care and establishing team-based care; 2) educating and empowering patients so that they are aware of the treatment plan and its advantages; 3) lowering the cost of medication, as well as lowering the barriers to accessing it. Education on hypertension, blood pressure self-monitoring, and frequent systolic blood pressure tests, as well as body weight and serum cholesterol impact on systolic blood pressure, are included in the instructional support. Importance of medication adherence. The real need for a healthy lifestyle with a heart-friendly diet.
	**Peer counseling (family member)**	• The counseling sessions are arranged face to face, and a specially developed module to change the beliefs of participants related to treatment outcome and medication adherence • This unique module is developed to change their beliefs related to poor lifestyle • The counseling sessions are geared toward overcoming the general obstacles related to medication adherence and poor lifestyle • The distinct feature of the counseling component centered on personal barriers • The involvement of family support will make it an effective tool • Counseling and encouraging participants to stick with their doctor and medication, even if they feel better. • Changing their behavior towards a healthy lifestyle • Proper medication adherence and adopting a healthy lifestyle eventually help them out in improving health-related quality of life
**mHealth intervention**	**Written and voice reminders**	• “It’s time for you to take your medicine.” • “This is to remind you that you need to take your medication.” • “How are you?” “Remember your appointment a day after tomorrow” • “How are you?” “Remember your appointment tomorrow”
	**Educational-led video**	• Awareness about hypertension • What causes uncontrolled hypertension • Consequences of uncontrollable hypertension • Effect of medication adherence on blood pressure • Effect of healthy lifestyle change on blood pressure • Effect of medication adherence and healthy lifestyle on quality of life • Relation of poor adherence (medication and lifestyle) with uncontrolled hypertension • Lifestyle changes for better health outcome, which enhances better health-related quality of life
**Combined intervention**	**Ed-counseling intervention**	Ed-counseling intervention + mHealth intervention
	**mHealth intervention**	

The first group will receive no intervention and only standard hospital care (as per the practice of the hospital); the second group will receive monthly Ed-counselling sessions in addition to standard care; the third group will receive daily written and voice reminders and once weekly an education-led video in addition to standard care; the fourth group will receive Ed-counselling sessions every month, daily written and voice reminders, and once weekly an education-led video in addition to standard care.

#### Educational support with peer counseling

Peer counseling sessions will be led by doctors who are specialized in hypertension. Patients and their families will be focused on these sessions. Face-to-face sessions will take roughly 20–25 min each. Patients will receive spoken and written instructions based on their abilities during these sessions. Counseling sessions are geared toward overcoming both general and personal obstacles. They will learn about the need of adhering to medicine, nutrition, and exercise regimens, as well as about the possible consequences of failing to do so (heart attack, stroke, nephropathy, retinopathy, and dementia). The counseling component also addresses personal barriers to taking medication and is designed to assist participants in better understanding their drug-taking attitude. The peer counseling sessions will take place four times for a total of twelve months, at 1, 4, 8, and 12 months. Information on hypertension, blood pressure self-monitoring, and frequent systolic blood pressure tests, as well as body weight and serum cholesterol values, are included in the instructional support. Food control, exercise therapy, hypertension problems, and their management will also be explored as non-pharmacological therapeutic approaches. Furthermore, based on their unique needs, patients will be informed about medicine administration timings and quantities. Finally, all patients will be informed about antihypertensive medications, including indications, side effects, contraindications, warnings/precautions, drug interactions, and pregnancy risks. Educational components will be delivered through educational booklets with animated infographics.

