### Sample size

For comparing different interventions among the four groups, the sample size is computed through the STATA software using a standard deviation of 18.5 in systolic blood pressure taken from a Pakistani study [9], population means of 148 and 143 respectively, as 5 mmHg reduction in systolic blood pressure is related to clinical importance regarding decreasing the risk of coronary artery disease [25]. A two-sided level of significance of 5% and a power of 90% with a 30% attrition rate between the baseline and 12 months of the intervention period were used. The total sample size calculated is 1648 with 412 in each group.

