### Statistical analysis

The intention-to-treat analytic method will be conducted [35, 36]. Mixed-effects modeling with repeated measures will be employed for the primary outcome change in systolic blood pressure at 0, 6, and 12 months. To estimate treatment effects at each time point, an interaction between time and the groups will be fitted. For the primary and secondary outcomes measuring systolic blood pressure and medication adherence difference between and with the group at 0, 6, and 12 months, parametric (ANOVA/repeated measure ANOVA) and non-parametric tests *(*Kruskal*-*Wallis test*/*Friedman test/Wilcoxon signed*-*rank test) will be used. We shall account for the multiple time points statistically by using Tukey’s exact test. The Tukey test will be utilized for multiple comparisons and adjustment for multiple comparisons will be performed by Bonferroni correction. All the outcomes will be analyzed at 0, 6, and 12 months; however, the final analysis will be at 12 months from baseline. The *p*-value for the significance test will be set at *p* < 0.05. Pill counting data, adherence assessment at dichotomous variables, frequencies, and the chi-square test will all be used. By using the general estimating equation (GEE) with negative binomial regression, at 12 months post-follow-up, the covariates affecting primary and secondary outcomes including, age, gender, ethnicity, living status, education, monthly income, use of reminder, health insurance coverage, body mass index (BMI), diabetes, duration of illness, number of comorbid conditions, number of daily medication use, dose frequency will be determined and controlled. A complete analysis plan will be established for data analysis, including subgroup analyses and sensitivity analyses.

Sub-group analyses of the change in systolic blood pressure, the adherence to medication over the previous 12 months will be conducted by age (21–29 years, 30–49 years, 50 years and above), sex (male, female), adherence (SEAMS, pill-counting), and health-related quality of life (using EQ-5D-3L and EQ-VAS). Missing data from attrition will be handled using a multiple imputations approach at 12 months.

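### Doctors deliver Ed-counselling in groups 2 and 4 only, but the 90% power allows nothing for clustering by doctor and the named analyses include no doctor term

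*Protocol article*

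**What the plan says.** The protocol article randomises patients individually to four groups of 412 (Abstract; Randomization and blinding). Groups 2 and 4 receive Ed-counselling and groups 1 and 3 do not (Intervention). On delivery, the section on educational support with peer counseling states: "Peer counseling sessions will be led by doctors who are specialized in hypertension". Sessions are face to face, last 20 to 25 minutes, and address each patient's own barriers. The article does not say how many doctors there are, how many patients each sees, or whether a patient stays with one doctor.

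The Sample size section uses a "standard deviation of 18.5 in systolic blood pressure taken from a Pakistani study", "population means of 148 and 143 respectively", and "A two-sided level of significance of 5% and a power of 90% with a 30% attrition rate between the baseline and 12 months". It mentions no design effect.

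For the analysis: "Mixed-effects modeling with repeated measures will be employed for the primary outcome change in systolic blood pressure at 0, 6, and 12 months". A time-by-group interaction is specified, and ANOVA, rank tests and chi-square tests are also listed. No doctor term is named. The random effects of the mixed model are not listed, and a fuller analysis plan is announced.

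**The concern.** Patients counselled by the same doctor share that doctor's skill and style, so their later blood pressures may be correlated. This can happen only in groups 2 and 4, which is what makes the design partially nested. A comparison of a counselled with a non-counselled group that ignores the correlation has too small a standard error, and a sample size that ignores it gives less power than stated. Good results from a few effective doctors could then be read as an effect of the module.

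The caseload is large. Two groups of 412 make 824 patients. With four sessions each, that is 824 x 4 x 20/60 = about 1,100 hours, up to 824 x 4 x 25/60 = about 1,370 hours. The Intervention section speaks of monthly sessions, while the peer counseling section gives four. Those two passages must be reconciled, but that is a separate point. Either way, many patients will probably share each doctor unless the doctors are numerous.

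**Working it through.** **Step 1: reproduce the plan's figure.** Inputs from the Sample size section: difference 148 - 143 = 5 mmHg, SD 18.5, two-sided 5%, power 90%, attrition 30%.

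n per group = 2 x (1.960 + 1.282)^2 x 18.5^2 / 5^2 = 288 after rounding up. Then 288/0.7 = 412 after rounding up, and 4 x 412 = 1648. Both stated figures are matched exactly with independent patients (design effect 1).

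**Step 2: power as planned.** Completers per group = 412 x 0.7 = 288.4. SE = 18.5 x sqrt(2/288.4) = 1.541. Power = Phi(5/1.541 - 1.96) = 90.1%.

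**Step 3: allow for clustering in the counselled group only.** Let K be the number of doctors and ICC the doctor intraclass correlation. Both are assumptions, because the article gives neither.

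- Patients per doctor in group 2: m = 288.4/K
- Design effect in group 2: DE = 1 + (m - 1) x ICC
- SE of group 2 minus group 1: 18.5 x sqrt((1 + DE)/288.4)
- Power: Phi(5/SE - 1.96)
- False-positive rate if clustering is ignored: 2 x P(Z > 1.96 x 1.541/SE)

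Worked case, K = 8 and ICC = 0.01: m = 36.05; DE = 1.35; SE = 18.5 x sqrt(2.35/288.4) = 1.670, which is 1.084 times the unclustered value. Power = Phi(2.994 - 1.96) = 84.9%. False-positive rate = 2 x P(Z > 1.81) = 7.1%.

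Group 2 against group 1:

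| Doctors (K) | ICC | SE factor | Power | False-positive rate if ignored |
|---|---|---|---|---|
| 4 | 0.01 | 1.164 | 79.6% | 9.2% |
| 8 | 0.01 | 1.084 | 84.9% | 7.1% |
| 16 | 0.01 | 1.042 | 87.6% | 6.0% |
| 24 | 0.01 | 1.027 | 88.5% | 5.6% |
| 4 | 0.05 | 1.667 | 49.5% | 24.0% |
| 8 | 0.05 | 1.370 | 65.9% | 15.2% |
| 16 | 0.05 | 1.194 | 77.6% | 10.1% |
| 24 | 0.05 | 1.129 | 82.0% | 8.3% |

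The last column applies only if doctor effects vary around a mean of zero. All figures use a normal approximation, so with very few doctors true power is lower than shown.

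**Step 4: the 2x2 main effect.** Groups 2 and 4 against groups 1 and 3 give 2 x 288.4 = 576.8 completers per side. If the same K doctors serve groups 2 and 4, m = 576.8/K. Under independence power is 99.6%. At ICC 0.01 it is 93.9% with 4 doctors and 97.6% with 8, but the SE is understated by factors of 1.310 and 1.164. At ICC 0.05 power is 57.3%, 78.6%, 91.8% and 95.5% with 4, 8, 16 and 24 doctors.

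**Step 5: other contrasts.** Group 3 against group 1 involves no counselling doctor. In group 4 against group 2, a doctor effect common to both groups largely cancels if the same doctors serve both.

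**The case against.** Several parts of the case on the other side stand.

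- **The model is not fully described.** A reader might infer that the primary model treats patients as independent. The article does not support that: it names a mixed model without listing its random effects and announces a fuller analysis plan, where a doctor effect may appear. The covariate list belongs to the GEE analysis, so the absence of a doctor variable there proves little. What remains is that no doctor term is named and that the stated 90% rests on independence. A later plan could correct the standard errors but not that power figure.
- **The number of doctors is unknown.** A reader might infer a small panel, but no number is given. With 40 doctors and ICC 0.01, power is 89.2%, an immaterial loss. Rotating doctors over sessions would also dilute the clustering.
- **ICC 0.05 is extreme.** It means a between-doctor SD of sqrt(0.05) x 18.5 = 4.1 mmHg, close to the whole 5 mmHg target. With a mean benefit of 5 mmHg, and doctor effects normally distributed, about 11% of doctors would raise blood pressure.
- **False-positive inflation is conditional.** If counselling does nothing for anyone, it creates no doctor variation and the test keeps its 5% level.
- **Baseline information may offset the loss.** With an assumed baseline correlation of 0.5, 8 doctors and ICC 0.01, the variance is 0.75 x 2 + 0.35 = 1.85 units against the 2 planned, and power is about 92%. This is fair, but without clustering the same model would have 1.5 units, and power Phi(5/(18.5 x sqrt(1.5/288.4)) - 1.96) = about 96%. Clustering still costs power, and an SE that ignores it is still too small.

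The high power of the factorial main effect is only a partial answer. Each doctor then contributes twice as many patients, so the SE is understated by more.

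**Conclusion.** The point holds in conditional form. It is documented that counselling is doctor-delivered in two groups only, that 412 per group contains no allowance for clustering by doctor, and that no doctor term is named in the analysis. It follows that, if the doctor ICC exceeds 0, the 90% does not hold for group 2 against group 1 on the plan's own inputs. An analysis without a doctor term would also understate the SE of counselled against non-counselled contrasts.

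The size depends on undocumented quantities. At an assumed ICC of 0.01, power for group 2 against group 1 runs from about 80% (4 doctors) to 88.5% (24 doctors). The false-positive rate is about 9% to 6% if doctor effects vary around zero. ICC 0.05 marks the upper extreme, at about 50% to 82% power.

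A reader might conclude that the Ed-counselling standard errors are certainly wrong or that the whole trial is underpowered. The article supports neither. The ICC and the continuity of doctor are unknown, mHealth against standard care is untouched, group 4 against group 2 is largely untouched if the doctors are shared, and the main effect keeps over 90% power in many scenarios. The change is worth making because it is cheap and because doctor identity, if not recorded, may not be recoverable later.

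**What to change.** 1. Record the counselling doctor for every patient in groups 2 and 4, at each session if the doctor can change.
2. In the SBP mixed model, add a doctor random effect that applies only in the counselled arms, with small-sample degrees of freedom. If there are very few doctors, report this model as a sensitivity analysis.
3. In the Sample size section, state that the 90% power assumes no clustering by doctor, and give power over a range of ICC for the actual number of doctors.

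The cost is one field on the session log, one model term and a restated power. No additional patients are needed, because the change qualifies the power claim and does not try to restore it. The downside is wider intervals for the counselled against non-counselled contrasts, and an imprecise doctor variance if doctors are few. With one doctor per hospital, that variance would also be hard to separate from differences in effect between hospitals.

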#### Involvement of patients and their families

A patient companion will be enrolled in the study for the duration of the trial and will participate in educational and counseling sessions. The objective of involving family members is to learn about their experiences with our Ed-counselling sessions.

#### mHealth intervention

The mHealth intervention will consist of daily written reminder messages and a video once a week. A professional Information and Technology (IT) facilitator will provide this intervention module. The IT facilitator will be responsible for overseeing the overall messaging, keeping track of it on the computer, and ensuring that all of the material for the various interventions is delivered on time. For the duration of the study, all participants will receive a free 12-month “WhatsApp” Internet connection.

A skilled IT team collaborated with two experts from one of the study hospital’s cardiology, hypertension, and nutrition departments in Lahore, Pakistan, to create educational animated infographic videos having both educational and counseling content. The content of the video is also based on the Health Beliefs Model. There are three parts to the video: (1) hypertension awareness, (2) uncontrollable hypertension’s consequences, and (3) improved health through medical and lifestyle improvements. The length of the video will be of 1 min.

Pilot testing among 10% of the total sample will be undertaken to guarantee that 165 people with hypertension and angina understood the video’s substance and message. These participants will be recruited from two of the study hospitals using the same criteria as indicated above. The results of this sample will not be included in the final analysis. As a result, these can be changed before the study. This will enable testing of the intervention and can establish if any errors occurred during the intervention’s delivery. It will also assist in identifying issues with eligibility requirements and determining the feasibility of obtaining a sufficient sample size.

Peer counseling and mobile health interventions are anticipated to help intervention group members adhere to their drug regimens and achieve the desired results. There are no limitations on concomitant care during the research.

### Follow-up

Subjects in all four arms of the study will be followed up, three times in 12 months following recruitment. Blood pressure measurement for treatment outcome will be done. The Self-efficacy for Appropriate Medication Adherence Scale (SEAMS) is an adherence-monitoring scale that will be used to collect information from participants regarding their adherence to medication self-reporting. Apart from SEAMS, self-reporting pill counting for measuring medication adherence will be used, and health-related quality of life using EuroQol 5-Dimension-3-level (EQ-5D-3L) and a visual analog scale (EQ-VAS) will also be assessed. All the above assessments will be done at baseline, 6 months, and 12 months of follow-up.

### Outcome measures

The primary outcome measure is the change in participants’ systolic blood pressure at 0, 6, and 12 months. It will be recorded by a nurse who will be oblivious to the study participants’ group. MODEL-605P YAMASU, a calibrated upper-arm mercury sphygmomanometer, will be utilized for this purpose. The blood pressure of the participant will be measured according to standard procedures. Two different readings will be collected within 5 min; the average measurement will be the final measurement. If the difference between the two measures is greater than 5 mmHg, a third evaluation will be performed, with the average of the two closest measurements being used as the final measurement [30].

In accordance with this, we are going to measure the proportion of participants who will achieve systolic blood pressure ≤ 140 mmHg. There are several secondary outcomes to be investigated. Health-related quality of life baseline, 6 months, and 12 months after the intervention will be measured via the EuroQol 5-Dimension- 3-level (EQ-5D-3L) [31, 32]. The five dimensions include mobility, self-care, normal activities, pain or discomfort, and anxiety or depression. Each dimension has three levels: no difficulty, moderate problems, and serious problems. In addition, we are using the EQ-VAS to measure the patient’s self-rated health on a vertical visual analog scale, with two unique endpoints such as “Best imaginable health condition” for a score of 100 and “Worst imaginable health state” for a score of 0 [31].

We will assess self-reported information regarding the number of tablets that will be utilized by participants within the specified timeline divided by the number of pills prescribed for that time multiplied by a hundred for the last 7 days. A rate of ≥ 80% will be considered adherent and vice versa [7, 8]; thereby, the percentage of participants who are successful in achieving adherent status between baseline and 12 months will be evaluated. In addition, to measure the adherence score at baseline, 6 months, and 12 months post-intervention, an Urdu/English version of the “Self-efficacy for Appropriate Medication Adherence Scale” (SEAMS) will be employed [33, 34]. The SEAMS is a 13-item measure for evaluating medication self-efficacy in chronic disease management that looks to be appropriate for people with low literacy abilities [34]. This survey will use a three-point response system, with 1 indicating lack of confidence, 2 indicating moderate confidence, and 3 indicating extreme confidence. The 13-item scale had a range of possible scores from 13 to 39. High scores indicate better adherence.

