In Pakistan, 18.9% of teenagers over the age of 15 years and 33% of adults over the age of 45 years suffer from hypertension [6]. Adherence is termed as “the extent to which individuals follow their healthcare providers’ prescribed drug schedules” [7]. Adherence to cardiac medications was reported at 77% [8], while non-adherence to antihypertensive medication was found among 37.7% of patients in Pakistan [9]. Thus, non-adherent patients constitute a significant proportion of the treatment population in the country. Also, the majority of individuals on antihypertensive medications had uncontrolled blood pressure and poor adherence to treatment which further compounds the dysregulation of an individual’s blood pressure [9, 10].mHealth is a term used for any medical and public health application supported by mobile phones, personal digital assistants, patient monitoring devices, or other wireless devices [11]. The use of mobile health interventions to enhance medication adherence has been reported to be effective, particularly in LMICs [12–14] as these provide results at a lowered cost [15]. Despite positive feedback reported on the effectiveness of mHealth interventions on adherence to medication in general, its role in cardiovascular medication adherence is under-studied especially in a scarcely resourced country like Pakistan. Moreover, in the context of behavior changes in response to the changing dynamics of disease, there is a need to compare mHealth intervention with different interventional methods to assess its effectiveness [16]. Similarly, the literature suggests that counseling therapy is also an effective strategy in modifying behavior regarding adherence to antiretroviral and anti-tuberculosis treatment [17–19]. Counseling was found to be an affordable intervention at the personal level in enhancing medication adherence [20] but its use in hypertension and cardiovascular diseases is limited.

There is a need for an efficient and cost-effective model to be adopted in LMICs like Pakistan, where there is a lack of resources (e.g., constraints on the public health budget) and where people have a generally poor educational status. Most of the interventions in improving medication adherence are not financially affordable besides having complex designs. It is therefore imperative to work on improving adherence to anti-hypertensive medications and altering behavior by designing cost-effective interventions with lesser intricacies.

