### Study participants and eligibility criteria

The study participants will be hypertensive patients with coronary artery disease as comorbidity registered in the Cardiology Outpatient Departments (OPDs) of four selected public teaching hospitals in Lahore, Pakistan.

Inclusion criteria include men and women over the age of 21 and up to 70 years, who have been registered for the last 30 days or more as hypertensive with comorbidity of coronary artery disease in the OPDs of the selected teaching hospitals in Lahore, Pakistan. These participants will be having stable coronary artery disease, are already on anti-hypertensive medication, are willing to sign a written informed consent form, possess a smartphone with access to the Internet, and are able to read Urdu/English.

Patients with a history of cancer who may need drug changes; with a blood pressure reading of more than 220/120 mmHg; with any biological condition that makes it difficult for them to read, write, communicate, or hear phone calls; with pregnancy and in lactation period; and who are enrolled in some other study will be excluded.

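### Two goal outcomes are worded as 'achieving' SBP ≤140 mmHg or adherence, but patients may enter already at goal; define both as 12-month status, adjusted for baseline

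*Protocol article*

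**What the plan says.** Under Study participants and eligibility criteria, the protocol article takes patients "who have been registered for the last 30 days or more as hypertensive" with stable coronary disease who "are already on anti-hypertensive medication". The only blood-pressure limit is an upper one, excluding those "with a blood pressure reading of more than 220/120 mmHg". There is no lower SBP limit, and adherence plays no part in entry.

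Under Outcome measures, beside the primary outcome (change in SBP), the trial will measure "the proportion of participants who will achieve systolic blood pressure" of 140 mmHg or less. For self-reported pill-taking with an 80% cut-off, "the percentage of participants who are successful in achieving adherent status between baseline and 12 months will be evaluated". Neither outcome names a denominator or mentions status at entry.

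Under Statistical analysis, dichotomous adherence gets frequencies and a chi-square test. No test is named for the SBP proportion. The regression paragraph lists 14 covariates; baseline SBP and baseline adherence are not among them, although the Follow-up section has both measured at baseline.

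**The concern.** Achieving a goal implies not being there before. A patient who enters at 130 mmHg and stays there would count as achieving control. On one reading, a patient who enters taking every pill would count as achieving adherence. If many participants are at goal at entry, the proportion in each arm, control included, will be read as success of treatment when much of it was already present.

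The adherence wording adds an ambiguity. It could mean status at 12 months in everyone, a change from non-adherent to adherent, or adherence at any visit. These are different estimands with different denominators, and a choice made after the data are seen would be open to selection. Baseline status, the strongest available predictor of 12-month status, is collected but used in neither outcome.

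**Working it through.** **Inputs.** From Sample size: "population means of 148 and 143 respectively", SD 18.5, two-sided 5%, power 90%, attrition 30%. From Background: "non-adherence to antihypertensive medication was found among 37.7% of patients in Pakistan", and 77% adherence to cardiac medication. Assumed: 148 is the baseline mean (the protocol does not label it so), normality, equal SDs, and a baseline-to-12-month correlation ρ of 0.5, 0.6 or 0.7.

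**The plan's own figure.** n = 2(1.96 + 1.2816)² × 18.5² / 5² = 287.7, so 288 per arm. Then 288/0.70 = 411.4, so 412, and 4 × 412 = 1648. The stated size is reproduced.

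**At goal at entry, SBP.** Φ((140 − 148)/18.5) = 33.3%, or about 548 of 1648 and 137 of 412 per arm. Truncation at 220 mmHg changes nothing. The share is 20.9% for a mean of 155 and 43.6% for a mean of 143. For SDs of 15 to 22 it is 29.7% to 35.8%.

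**At goal at entry, adherence.** 100 − 37.7 = 62.3%, or 77% on the cardiac-medication figure. That leaves 23–38% who could newly become adherent.

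**At goal at 12 months.** Control stays at 148: 33.3%. Active at 143: Φ((140 − 143)/18.5) = 43.6%.

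**By entry status (bivariate normal).**

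| | ρ = 0.5 | ρ = 0.6 | ρ = 0.7 |
|---|---|---|---|
| 12-month achievers already at goal at entry, control | 54.8% | 59.9% | 65.5% |
| same, active | 50.6% | 54.6% | 58.9% |
| Entered >140, at goal at 12 months, control v active | 22.5 v 32.2% | 20.0 v 29.6% | 17.2 v 26.8% |
| Arm difference, entered >140 | 9.7 points | 9.6 points | 9.6 points |
| Entered ≤140, still at goal at 12 months, control v active | 54.8 v 66.3% | 59.9 v 71.5% | 65.5 v 77.2% |
| Arm difference, entered ≤140 | 11.5 points | 11.6 points | 11.6 points |

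At ρ = 0.3 the first two rows are 46% and 43%.

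**Power for SBP ≤140, one active arm against control.**
- Unadjusted, 288 per arm, 33.3% v 43.6%: 72%. This does not depend on ρ.
- Only those above 140 at entry, 288 × 0.667 ≈ 192 per arm: 57%, 59% and 62% for ρ = 0.5, 0.6 and 0.7.
- All participants, logistic regression with baseline SBP as covariate, by simulation: about 80% to 87%. One set of 2,000 runs per correlation gave 80%, 81% and 86%.

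No power is given for adherence, because the protocol states no effect size for it.

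**The case against.** A reader might infer that patients at goal at entry cannot respond, and so dilute the effect and cost power. The protocol's own planning figures do not support that. Such patients can lose control, and treatment can prevent the loss: their arm difference is 11.5–11.6 points, slightly larger than the 9.6–9.7 points in those above 140. Restricting the analysis to those above 140 lowers power from 72% to 57–62%. The gain from adjustment comes from using a prognostic covariate and would be available under any entry criteria.

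Nor is there bias. Randomisation balances entry status on average, and each active arm is read against a concurrent control. Enrolling all treated hypertensive patients is a legitimate pragmatic choice.

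It can also be said that the plan goes part of the way. All outcomes are to be analysed at 0, 6 and 12 months, so baseline proportions should be visible. Adherence is listed as a subgroup factor, and a fuller analysis plan is promised. The first point softens the risk of misreading. The subgroup entry does not say that it means baseline adherence. A covariate can be left to the analysis plan, but what an outcome counts, and in whom, is fixed by the protocol, and here the wording does not fit the population enrolled.

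The magnitudes rest on planning and cited-population values. The Background also says that most treated patients had poor adherence, which sits uneasily with its own 37.7%.

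**Conclusion.** The point holds as one of definition and efficiency for two non-primary outcomes. On the protocol's figures about a third of participants (21–44%) may enter at or below 140 mmHg, and 62–77% may enter adherent. More than half of the 12-month SBP achievers in each arm would then have been at goal before treatment, if the correlation is 0.5–0.7. The raw proportions are valid for comparing arms but are not rates of new achievement, and the adherence outcome admits more than one estimand. Baseline adjustment is a nearly free improvement on the chi-square test stated for adherence, and on the unstated analysis for SBP. The primary outcome and the sample size of 1648 are not affected. The sizes depend on taking 148 as the baseline mean, on normality, and on the assumed correlation; the adherence share depends on background rates from other populations.

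**What to change.** - Define both outcomes as status at 12 months in all randomised participants: SBP ≤140 mmHg, and pill-taking ≥80% (the cut-off given under Outcome measures).
- Analyse each by logistic regression on arm with its baseline value as covariate. For adherence this replaces the unadjusted chi-square test. For SBP it supplies an analysis where none is named.
- Report the raw proportions at baseline and at 12 months by arm beside the odds ratio, since the adjusted odds ratio is conditional on baseline.
- Keep the word *achieved* for a pre-specified descriptive table of conversion among those not at goal at baseline, with its denominator. That subset is about 67% of participants for SBP and 23–38% for adherence, and its power is lower, so it should not carry the inference.

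The cost is the wording of two outcomes and a small analysis change with data already collected. Eligibility, visits and sample size stay as they are.
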